#### Control condition

Mother-child dyads in the control group receive a factsheet information brochure on youth alcohol use and the detrimental consequences of alcohol use among children, which is the standard alcohol brochure of the Trimbos Institute. Providing a brochure for controls was done primarily to establish a plausible explanation regarding the need for the post-treatment survey for participants in the control condition. The brochure will give them the idea that they are participating in an alcohol prevention study. We choose for this brochure, because it is already available for all Dutch parents, and can be found in several health institutions. It is easily accessible for parents who have an interest in youth alcohol use, so basically many Dutch parents were already exposed to this type of prevention. Although this information could increase mothers' knowledge regarding alcohol issues, this knowledge is not expected to have an effect on alcohol-specific socialization processes or on children's susceptibility to or initiation of alcohol use, since it will not include any tools for mothers on how to use alcohol-specific parenting.

### Data Collection

Both mothers and children will receive separate personal login codes by email. With these login codes they have access to their own baseline questionnaire on a secured webpage. In the case a mother or child prefers a paper questionnaire, this will be sent to their home. Mothers and children are explicitly asked to fill in the questionnaires separately. This questionnaire procedure will take place at each assessment. Non-responding mothers or children will be approached by phone to motivate them to fill in the questionnaire. Mothers and children in both the experimental and control condition will be assessed at baseline (1 month before prevention starts), after 6 months (first follow up), after 12 months (second follow-up) and after 18 months (third follow up). An overview of all measures at each time point is provided in Table 1.

**Table 1 T1:** Overview of Measures

Measure	Baseline		Follow-up 1		Follow-up 2		Follow-up 3	
	Mother	Child	Mother	Child	Mother	Child	Mother	Child
Demographic characteristics	X	X						
Monitoring	X	X	X	X	X	X	X	X
Parent-child relationship (NRI)		X		X		X		X
Intention to drink alcohol		X		X		X		X
Self-efficacy		X		X		X		X
Drinking norms		X		X		X		X
Alcohol use parents	X	X	X	X	X	X	X	X
Problem drinking parents	X		X		X		X	
Alcohol use child	X	X	X	X	X	X	X	X
Alcohol use peers & siblings		X		X		X		X
Attitude about alcohol	X	X	X	X	X	X	X	X
Alcohol-related consequences	X	X	X	X	X	X	X	X
Anti alcohol socialization								
Availability of alcohol at home	X	X	X	X	X	X	X	X
Rules on alcohol	X	X	X	X	X	X	X	X
Communication about alcohol	X	X	X	X	X	X	X	X
Parental norms	X		X		X		X	
Parental influence on offspring alcohol use	X		X		X		X	
Strengths and Difficulties Questionnaire (SDQ)	X	X	X	X	X	X	X	X
Program evaluation/utilization			X	X				

#### Outcomes

The primary outcome, initiation of alcohol use, is defined as have been drinking at least one glass of alcohol. Secondary outcome measures are alcohol-specific parenting dimensions such as rules about alcohol, non-drinking agreement, alcohol availability at home, and frequency and quality of alcohol-specific communication (e.g., [7,26]), but also general parental monitoring [27] and parent-child relationship quality [28]. Other outcomes are susceptibility to drinking alcohol, defined as the lack of a firm commitment against drinking alcohol [29,30], alcohol expectancies [31], self-efficacy [32,33], and frequency and intensity of child alcohol use [34]. The Strengths and Difficulties Questionnaire (SDQ) [35] will be used as a behavioral screening instrument for early detection of psychological problems. Psychological problems are associated with problem behaviors like drinking alcohol at an early age (e.g., [36]).

#### Statistical analyses

In accordance with the intent-to-treat philosophy, all children randomized to a condition will be included in the analyses to test the study hypotheses. Moreover, while randomization takes place on school level and children are 'nested' within these schools, we need to control for clustered data [37]. Mplus is a statistical modeling program that has special features to deal with missing data and it allows analyses with complex data while taking into consideration the longitudinal character of the data and the fact that data are clustered. Regression analyses for dichotomous outcome measures (logistic regression) will be conducted to test whether children in the control condition are more likely to initiate drinking than children in the experimental condition [14,37]. For the second aim of our study, namely, that mothers in the prevention group will use more alcohol-specific socialization strategies than mothers of the control group, we will perform mediation analyses in Mplus, using the bootstrap method [37]. To test our third hypothesis of the study, possible moderating effects of relevant demographic indices such as gender, as well as mothers' alcohol use at baseline, we will create products of the predictors and then include those interaction terms in the logistic regression model (e.g., condition * mothers' drinking; [37]).

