## Background

Adolescence is characterized by a strong increase in alcohol use: In 2009, approximately 40% of all Dutch 12-year olds reported lifetime alcohol use, which increases to 70% among 14-year olds and 85% among 16-year olds [1]. Of the Dutch 12-year olds, 9.7% even reported to have been drinking in the last month [1]. Starting to drink at an early age puts youth at serious risk of developing many alcohol-related problems, such as heavy episodic drinking, alcoholism, and cognitive impairments (e.g., [2,3]). These consequences of early onset of alcohol use stress the need to postpone the age of onset. Most school-based alcohol prevention in the Netherlands is conducted at the secondary educational level among 12-15-year olds, while at this age many children have already started to experiment with alcohol. Since many Dutch youth start to drink in early adolescence, prevention programs targeting elementary schoolchildren are needed. However, theory-driven alcohol prevention programs for elementary schoolchildren are lacking.

Socialization theory [4] posits that parents are the main socializing agents in their children's development, especially when it comes to health issues, which has been supported by a wide range of studies [5,6]. Recent studies in the Netherlands showed that through e.g., setting strict rules about alcohol, communicating constructively about alcohol issues, and monitoring daily activities, parents can delay the onset of alcohol use [7-10]. Another reason why parents are important in preventing adolescent alcohol use is that elementary schoolchildren live at home and are still very susceptible to their parents' influences, while peers become more important during mid-adolescence and in some domains parental influence declines [9,11]. Moreover, most children get their first glass of alcohol from their parents [12]. By making parents aware of their role in introducing alcohol to their child, the age of alcohol onset can be delayed (e.g., [8]).

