#### Inclusion criteria

To be included in the present study, children will have to be in grade 6 of Dutch elementary school, when most children are 11-12 years old. Children can only participate together with their mother or a female guardian, and they both have to be able to speak and read Dutch. The form with which mothers and children sign up for the study also serves as an informed consent form. The proposed study and prevention protocols have been approved by the ethical committee of the Faculty of Social Sciences at the Radboud University Nijmegen (ECG16092010).

We focus on grade 6 children (11-12 years old) at baseline, because children start to get increasingly interested in alcohol issues at this age [18], but have generally not drunk their first glass of alcohol yet [19], which makes them an important target group for primary prevention. Providing an alcohol prevention program just before the age of onset, might have a large impact on the health of these children [8]. Inclusion of younger children might not be appropriate, because they will be less likely to consider drinking alcohol themselves. Thus, the period will be too long before they think of trying alcohol. Further, this age group consists of children who are in late childhood, prior to early adolescence. Early adolescence is characterized by increased conflicts with parents, especially with mothers [20] leading to less conformity and openness. This pleads for a focus on the developmental period prior to early adolescence - late childhood - when children are expected to be still quite susceptible to the influence of their parents [21]. While Dutch prevalence figures indicate that 13 to 17% of the 11 years old children drank at least one glass of alcohol [19,22] and we expect this also to be the case in our sample at baseline, we expect that the prevention program "In control: No alcohol!" will significantly lower the increase of this percentage a year later.

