### Sample Size Calculation

Based on the outcomes of parent-adolescent interventions in the Netherlands and the United States [14,21], we expect a minimal 10% difference in initiation rates between the control and experimental group at the third follow up, which is approximately 12 months after the end of the prevention. Equal cell sizes are assumed for study cells and power of .80 has been targeted. The primary hypothesis, a significant lower percentage of children who have their first glass of alcohol in the prevention group than in the control group, will be tested at an overall significance level of 0.05 (two-sided). G-Power was used to calculate the estimated sample sizes for two-sample comparison of proportions. Based on the prevalence of alcohol use in 13 year olds (age of the children at 18 months follow-up), which is 55%, we need 404 children per condition. However, if we take into account possible attrition (0.80), the fact that data are clustered (mother-child dyads are nested within schools) and the fact that we apply multiple imputation in the case of missing data (factor 1.4), we end up with 656 children per condition ((183/0.80) * 1.4)). Thus, 1312 mothers (and children) are required to participate. In accordance with the intention-to-treat philosophy, all children randomized to one of the conditions are included in analyses to test the study hypotheses.

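### The primary initiation test keeps children who have already drunk a glass at baseline, which gives up power and leaves the target quantity unclear

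*Protocol article*

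**What the plan says.** - **Outcome** (Protocol article, Outcomes): "The primary outcome, initiation of alcohol use, is defined as have been drinking at least one glass of alcohol". This is a lifetime status; once met, it stays met.
- **Baseline drinkers** (Inclusion criteria): "While Dutch prevalence figures indicate that 13 to 17% of the 11 years old children drank at least one glass of alcohol", and the authors add "we expect this also to be the case in our sample at baseline". Eligibility rests on school grade, a participating mother or female guardian, and Dutch language. Never having drunk is not required.
- **Analysis set** (Statistical analyses): "all children randomized to a condition will be included in the analyses to test the study hypotheses". The Sample Size Calculation repeats the rule: "all children randomized to one of the conditions are included in analyses to test the study hypotheses". The primary model is a logistic regression. No restriction to never-drinkers and no adjustment for baseline drinking is stated.
- **Planning values** (Sample Size Calculation): a 10-point difference, described as one in initiation rates; a 55% rate, described as the prevalence of alcohol use at age 13; two-sided 0.05; power 0.80; 404 children per condition before inflation.
- **Data** (Data Collection, Table 1): child alcohol use is asked of mother and child at baseline, one month before the programme starts.

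**The concern.** Initiation is an event that only a child who has not yet had a glass can experience. By the authors' own expectation, about one child in seven enters the trial with the outcome already present. These children count as positive in both arms whatever the programme does. They pull the two percentages together and contribute nothing on onset.

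The planning values also mix two quantities. The effect is worded as a difference in initiation rates, while the 55% is a population prevalence that includes early starters. A reader cannot tell whether the 10 points are meant among all children or among those who can still start.

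At stake are the power of the primary test and the meaning of the headline result.

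**Working it through.** **1. The plan's own figure.** For 55% against 45%, two-sided 0.05, power 0.80, the pooled two-proportion formula is

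n = [1.96·√(2·p̄(1−p̄)) + 0.8416·√(p₁(1−p₁) + p₂(1−p₂))]² / (p₁−p₂)²

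With p̄ = 0.50 this gives (1.386 + 0.592)² / 0.01, so n = 392. With continuity correction it is 412. Exact enumeration of the two-sided Fisher test at n = 404 gives power 0.8001. The stated 404 is therefore reproduced for 55% against 45%. The z-test power at 404 is 0.81 and is used below.

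**2. Effect of baseline drinkers.** Let b be the share who have had a glass at baseline and p the rate of new onset among the rest. Then

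all-children rate = b + (1−b)·p, so all-children difference = (1−b) × difference among never-drinkers.

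For b = 0.13 to 0.17 the multiplier is 0.87 to 0.83. If 55% is the all-children control rate and b = 0.15, new onset among never-drinkers is (0.55 − 0.15)/0.85 = 47.1%.

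**3. Power at 404 analysed per arm, b = 0.15.** Never-drinkers per arm: 404 × 0.85 = 343. Ranges for b = 0.13 to 0.17 are in brackets.

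| Reading of the planning values | All children | Power | Never-drinkers only | Power |
|---|---|---|---|---|
| A. 55% and the 10 points both refer to all children | 55% vs 45% | 0.81 | 47.1% vs 35.3% (11.8 points) | 0.88 (0.87–0.89) |
| B. 55% refers to all, the 10 points to never-drinkers | 55% vs 46.5% (8.5 points) | 0.68 (0.70–0.66) | 47.1% vs 37.1% | 0.76 (0.76–0.75) |
| C. 55% and the 10 points both refer to never-drinkers | 61.75% vs 53.25% | 0.69 (0.70–0.67) | 55% vs 45% | 0.75 (0.76–0.74) |

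The smaller, restricted set has more power in every row. Under A, the programme has to achieve 11.5 to 12.0 points among never-drinkers to produce 10 points overall. Under B, 80% power needs 542 per arm with everyone kept. With restriction it needs 382 never-drinkers per arm, that is 382/0.85 = 450 children.

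**4. Baseline imbalance.** Differentiating b + (1−b)·p with respect to b gives 1 − p. At p = 0.471 this is 0.529, so each percentage point of chance imbalance in baseline drinking shifts the all-children contrast by about half a point. With schools as the randomised unit, such imbalance is more likely than with individual allocation.

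**5. Restriction against adjustment.** Take reading A: 343 never-drinkers per arm with 161 and 121 events, plus 61 baseline users per arm, all positive.
- Never-drinkers only: log-OR = ln(121/222) − ln(161/182) = −0.484; SE = √(1/121 + 1/222 + 1/161 + 1/182) = 0.156.
- All children, with baseline use as a covariate: log-OR −0.484, SE 0.156.

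The coefficient for baseline use diverges, but the condition effect is finite and identical.

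**6. Sensitivity to n.** The final 656 per condition does not follow from 404, since 404/0.80 × 1.4 = 707; this is a separate matter. Working back from 656 gives 656 × 0.80/1.4 = 375. At 375 and b = 0.15, power is 0.78 against 0.86 under A and 0.64 against 0.73 under B. The direction is the same.

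**The case against.** The strongest defence is that the plan is coherent if initiation is read as cumulative status. Hypothesis (a) in Aim and hypotheses concerns the percentage who will have had a first glass by the last follow-up. The outcome definition agrees. The 55% includes early starters and is applied to a sample that includes them. The authors foresaw baseline drinkers and describe a universal programme, for which prevalence among everyone offered it is a legitimate target. Under randomisation the comparison is unbiased. Covariates are commonly left to an analysis plan that is not shown here.

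Most of this stands, and it rules out several stronger conclusions that a reader might draw:
- *That hypothesis (a) goes untested.* It does not; the wording in Aim and hypotheses is cumulative.
- *That the test falls short of its planned power.* Under reading A the nominal 0.81, before clustering, is kept, and the loss is only power forgone.
- *That a baseline covariate would fail through separation.* Step 5 of the working shows that the condition estimate is unaffected.
- *That 40% of the sample are baseline drinkers.* The Background does say "approximately 40% of all Dutch 12-year olds reported lifetime alcohol use", but it does not define this as one glass, and the authors' expectation for their own sample is 13 to 17%.

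The defence does not remove the ambiguity over which population the 10 points describe, or the loss of power. Intention-to-treat does not require keeping these children either. Baseline use is recorded before the programme starts, so a restricted analysis by allocated condition respects the randomisation.

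**Conclusion.** The point holds as a cheap gain in power and clarity. It is not a flaw that invalidates the trial. At the authors' own baseline figure of 13 to 17%, keeping baseline drinkers shrinks the risk difference by 13 to 17% of its value. At 15% baseline users it costs about 7 to 8 points of power under readings A and B (0.81 against 0.88, or 0.68 against 0.76).

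The figures rest on these assumptions:
- 404 children analysed per arm.
- No clustering, because no intraclass correlation is given. True power is lower in both analyses.
- Children who report a glass at baseline still report one at 18 months. Inconsistent self-report would soften both the dilution and the exact equivalence in step 5.
- Baseline answers do not depend on the allocated condition.

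**What to change.** 1. Make the primary analysis first glass by 18 months, by allocated condition, among children reporting no glass at baseline. State how mother and child reports are combined for this purpose. Alternatively, keep all children and adjust for baseline use, which gives the same condition estimate and standard error when baseline users stay positive.
2. Keep lifetime use in all randomised children as a sensitivity analysis.
3. State whether the 55% and the 10-point difference refer to all children or to new onset among baseline non-users.

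The cost is a change of wording before outcomes are seen, with no new data. The downside of restriction is that about 13 to 17% of children leave the primary analysis set, and the primary result then describes never-drinkers rather than everyone offered the programme. The sensitivity analysis covers the wider group.

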We have a few reasons to focus on mothers as target parents: (a) most children spend more time with their mother than with their father, giving mothers the practical advantage of having more time to deliver the alcohol-specific socialization program to their children [23], (b) if parents are divorced, in most cases children live with their mothers [23], (c) women generally are more likely than men to enroll in health-related programs [24], (d) the smoking-specific program also included only mothers, and (e) given the plausibility that program effects would differ by parent gender, including fathers would substantially increase the size and costs of the proposed trial. However, since fathers drink more alcohol than mothers [23], we measure paternal drinking behaviors in the questionnaires of both mothers and children, to be able to control for paternal drinking in the analyses.

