#### Prevention condition

The proposed program, "In control: No alcohol!", consists of 5 modules which families receive by mail every 4 weeks for a period of 5 months. A module consists of an attractive magazine including information, games, quizzes, and puzzles for parents and children to complete together. These structured interactions for the parent and child is a key technique for facilitating parent-child engagement in the program. The magazines' content is based on the empirical evidence of alcohol-specific parenting in the delay of early alcohol intake (e.g., [7-9,26]).

Each of the five magazines addresses different important issues regarding youth alcohol use and child socialization. Magazine 1 consists of general information about alcohol, alcohol use among children and the importance of parenting behavior, such as anti-alcohol norms and parental supervision. Magazine 2 addresses the risks of alcohol use, especially among children, and parental attitudes towards early drinking. Magazine 3 focuses on parental modeling of alcohol use and the effectiveness of setting rules about alcohol, also for parents who use alcohol themselves. Magazine 4 aims at enhancing awareness about peer influence and increasing the ability to handle peer pressure, while magazine 5 discusses the influence of alcohol-related media and again stressed the eminence of setting clear and strict rules. In addition to these specific topics, each magazine contains general information and practical tips on high-quality parent-child communication in order to gradually increase parents' skill and comfort level in communicating with their children about alcohol.

In addition, with the first magazine the child receives a personalized activity book ("Logboek"). The activity book provides the child the opportunity to repeat what he/she learned about alcohol in a playful and personal way. It is also an extra stimulus to be active in the program. With the activity book, each child receives a personal login code for the related secured website http://www.houvolgeenalcohol.nl. The login code provides access to more games, puzzles and pictures related to the prevention program. The child can download the completed website activities and put them in his/her activity book, so he/she can create his/her own glossy journal.

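### The primary logistic regression names no baseline covariate, although control for paternal drinking is foreseen elsewhere; the test is valid, but some precision is forgone and the two sections need reconciling

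*Protocol article*

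**What the plan says.** Under Statistical analyses, the primary test is described in one sentence: "Regression analyses for dichotomous outcome measures (logistic regression) will be conducted" to see whether control children are more likely to start drinking. The same section commits to intention to treat and to handling clustering by school in Mplus. Child gender and the mother's baseline drinking appear there only as moderators; the plan is to form products with condition and "include those interaction terms in the logistic regression model". Paternal drinking is not mentioned in that section.

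Under Inclusion criteria, where the focus on mothers is justified, the article says that fathers' drinking is measured "to be able to control for paternal drinking in the analyses". It does not say which analyses, or which wave's value.

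Table 1 lists demographics at baseline. It lists the child's intention to drink, parental alcohol use, peer and sibling alcohol use and the SDQ at baseline and at every follow-up. Under Prevention condition, "Magazine 3 focuses on parental modeling of alcohol use". Under Randomization, whole schools are allocated, and no stratification or matching is mentioned.

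**The concern.** Two parts of the article do not meet. One gives controlling for paternal drinking as the reason for collecting it. The section that sets out the analyses for all three aims does not take it up. Whether the primary result is adjusted, and for what, is therefore not settled in the text.

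Three things are at stake, in order of weight:

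- **Prespecification.** Unless the model is fixed elsewhere, the choice between an adjusted and an unadjusted primary result stays open until data are seen.
- **Timing of the covariate.** Parental drinking is measured at all four waves, and one magazine addresses parental example. A follow-up value may be affected by the programme, and conditioning on it could remove part of the effect. The mother's drinking is tied to baseline where it is a moderator; the father's has no stated timing.
- **Precision.** Prognostic baseline data will already be in hand. Using them costs nothing in data collection and usually sharpens the comparison.

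**Working it through.** **Inputs from the article (Sample Size Calculation).** Two-sided alpha 0.05, power 0.80, equal arms, 55% reference rate, 10-point difference, 404 per condition before inflation, attrition factor 0.80, factor 1.4 for clustering and multiple imputation together, 656 per condition.

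**The plan's own figure.** For 55% versus 45% the pooled-variance formula gives 392 per arm, or 412 with continuity correction. The stated 404 lies within 3% of both and has 81.2% power with no covariate. The final 656 does not follow from either printed base: 404/0.80 × 1.4 = 707 and 183/0.80 × 1.4 = 320. That is a separate matter. I take 656 as given.

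**Unadjusted power at 656.** Effective n per arm = 656 × 0.80/1.4 = 374.9.
Power = Φ[(0.10√n − 1.96√(2 × 0.5 × 0.5)) / √(0.55 × 0.45 + 0.45 × 0.55)].
With n = 374.9: (1.936 − 1.386)/0.7036 = 0.782, so power is 78.3%.

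**Gain from one baseline covariate.** The covariate is standard normal and its log odds ratio per SD is an assumption. R² is the variance of the predicted risk divided by 0.5 × 0.5. The approximation replaces n by n/(1 − R²) in the formula above. As a check I simulated 6,000 trials per row with 375 children per arm, marginal rates 55% and 45%, and no school structure. The Monte Carlo SE of each power is √(0.79 × 0.21/6000) ≈ 0.005.

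| Log-OR per SD (assumed) | AUC | R² | Approximation | Simulation, unadjusted → adjusted |
|---|---|---|---|---|
| 0.5 | 0.63 | 0.056 | 78.3% → 80.6% | 78.6% → 80.0% |
| 0.8 | 0.70 | 0.124 | 78.3% → 83.4% | 79.2% → 83.3% |
| 1.0 | 0.74 | 0.174 | 78.3% → 85.5% | 78.9% → 85.4% |

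Like for like, the gain is about 2, 4 to 5, and 7 points.

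**Scale of the odds ratio.** The marginal odds ratio, control versus programme, is (0.55/0.45)/(0.45/0.55) = 1.49. Holding the marginal risks at 55% and 45%, the covariate-conditional odds ratio is 1.53, 1.58 and 1.62 in the three rows. The effect on risk is the same in all of them, which is why adjusted risks should accompany an adjusted odds ratio.

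**The case against.** The strongest reply is that the article never says the model is unadjusted. It is a condensed report, a covariate list is commonly left to the full protocol or analysis plan, and the statement on paternal drinking suggests that some adjustment is intended. That stands. A reader might infer that the plan fixes a model with condition as its only term; the text does not support this. It names no covariate, which is a weaker statement.

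Three other strong readings also fail:

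- **That chance imbalance between schools biases the test.** The plan commits to handling clustering, and under school randomisation a cluster-adjusted standard error already reflects chance imbalance. The size is also modest. With 15% baseline ever-use (the article expects "13 to 17% of the 11 years old children drank at least one glass of alcohol") and all of the 1.4 factor taken as design effect, the SD of the between-arm difference is √(2 × 0.15 × 0.85 × 1.4/656) = 2.3 points. If baseline drinkers all count as drinkers at follow-up and the overall rate is 50%, the rate among the others is (0.50 − 0.15)/0.85 = 0.412. A 1-SD imbalance then moves the follow-up difference by 2.3 × (1 − 0.412) ≈ 1.4 points, against an expected 10.
- **That the plan adjusts for follow-up parental drinking.** No section says so. Measuring it at every wave is not adjusting for it. A baseline-only rule is a safeguard, not the correction of a stated error.
- **That the trial is underpowered unless it adjusts, or that adjustment lifts power from 0.78 to 0.84 at AUC 0.70.** The sample size takes no credit for covariates, and 404 per arm has adequate power without them. The 78.3% arises because 656 does not follow from 404. The like-for-like gain at AUC 0.70 is 4 to 5 points.

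What the reply does not remove is the mismatch: a purpose stated in one section is not carried into the section that should act on it.

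**Conclusion.** The point holds as a minor one. The primary analysis names no baseline covariate while another section foresees controlling for paternal drinking, and the two should be reconciled. The clustered test on condition is valid as written. Prespecified baseline adjustment would be the better method, worth about 2 to 7 points of power.

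That range rests on an assumed covariate strength (log-OR 0.5 to 1.0 per SD), on 375 effective children per arm, on 55% versus 45%, and on treating clustering only through the effective sample size. The article gives no prognostic strength and no intraclass correlation. If the covariates predict initiation only weakly, the gain is close to nil.

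**What to change.** In Statistical analyses, state the primary model as condition plus a short baseline-only set, with school clustering. A workable set from data already collected is child age and sex, baseline intention to drink, and baseline maternal and paternal drinking. Then:

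- Say explicitly that this is the control for paternal drinking foreseen under Inclusion criteria, and that no follow-up value of parental drinking enters the primary model.
- Report the unadjusted clustered result as a sensitivity analysis.
- Report adjusted risks in each arm, and their difference, beside the odds ratio.

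Baseline ever-use is left out of the set on purpose. Because "initiation of alcohol use, is defined as have been drinking at least one glass of alcohol", a child who has already drunk has the outcome by definition, so ever-use as a plain covariate would predict it perfectly in that subgroup. How baseline drinkers are handled needs its own decision.

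The cost is a few sentences of text and no new data. The one small drawback is that the adjusted odds ratio is conditional and will tend to lie further from 1 than the unadjusted one; the adjusted risks deal with that.
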